### Tobacco smoking cessation

2.18

The immediate reduction of the number of people who smoke is of huge importance for Māori and one of the key health targets for the Ministry of Health NZ. Adult smoking rates for Māori are 21.3%, higher when compared with other ethnics groups such as Pacific (18.1%), and European/Other (7.9%) (35). It is clear that parental or household smoking increases children's risk of developing respiratory infections, which commonly result in hospital admissions (36).

For this endpoint (hypothesis 4), we will use the proportion of parent/caregivers where a referral to stop smoking services was made during the hospitalisation period for cessation services. This will be calculated by sending a list of parent/caregiver NHI numbers of all participant parent/caregivers to the sole face to face smoking cessation provider (Once and For All). The provider will then confirm if a referral had been received for that NHI number during the period of hospitalisation or within 30 days of discharge from hospital for the index admission.

### Referral to the Whare Ora healthy homes service

2.19

It is well established that good housing is particularly important for the first 9-months of life (37). The Growing Up In New Zealand study showed that poor housing was strongly associated with adverse health outcomes, even when controlling for income (37). Healthy homes initiatives have been shown to reduce acute hospital admissions in a NZ setting (26). The Whare Ora programme is a Waikato Healthy Homes initiative that was developed in 2016 to help whānau to create healthier, warmer, safer and drier homes. The service is free to eligible whānau and provides healthy homes education, products such as curtains, heaters, dehumidifiers and draught stoppers, and referral of families for further services by other providers (38).

Hypothesis 5 examines the difference between intervention and UC groups in the proportion of children for whom a Whare Ora referral was made within 30 days post-discharge. This will be calculated simply as the number of Whare Ora referrals in each group divided by the total number of eligible households (as some participants live in the same household) in that group. Any household can be counted only once in the numerator.

### Cumulative length of stay

2.20

Hypothesis 6 will compare differences between intervention and UC groups in median cumulative length of stay (LOS) in acute hospital admissions in the 12 months following discharge. Only coded events with lengths of stay of 3 h or more will be included in the calculation. Length of stay will be calculated in hours from the time of admission to the time of discharge using the hospital time stamp records. Length of stay will be calculated using, where appropriate, the rules established in the Ministry of Health's LOS indicator. These join events within the same districts where there is a transfer between the two and the second event commences less than 24 h after the end of the prior event. In these cases, if the initial admission is not acute then this and any length of stay in a joined subsequent hospitalisation, even if acute, will not be counted. Hospitalisations where none of the contributing stays is case-mix coded will also therefore be excluded, consistent with these rules. This endpoint will be calculated as the difference in median cumulative lengths of stay by individual (i.e., not summing for the group as a whole) and will include acute hospital stays at any hospital in the Waikato region. Using medians and individual level data will avoid outlier cases with very long lengths of stay having undue influence on the result of the test.

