As in other parts of Aotearoa, persistent, unfair and unjust inequities in access to material resources and health outcomes exist between communities in the Waikato region of NZ (4, 7). As in other parts of the country, the greatest inequities in resources and outcomes lie between the Indigenous and non-Indigenous populations. This is also true for the paediatric population. More than a quarter of Māori in the Waikato live in the most socioeconomically deprived area (Quintile 5), according to the NZ Deprivation Index (8). In 2013, two in five Māori children lived in households with low equivalised annual household incomes (under $15K) (8). This unequal distribution of wealth is a major driver of inequities in child health outcomes. Even after accounting for unequal distribution of wealth, stark inequities in hospitalisations between tamariki Māori and non-Māori remain. Only ten percent of children aged 0–4 years in Waikato are tamariki Māori, yet tamariki Māori accounted for 44% of hospital admissions for children aged 0–4 years in the winter months of 2014 (9). Of these children, most (71%) were admitted to hospital with a preventable medical condition that had a social gradient, meaning that children from areas of low deprivation had lower disease rates than those from higher deprivation areas (9). These diseases included acute bronchiolitis (43% of the winter admissions in this age group in 2014), pneumonia (11%), asthma (6%) and acute upper respiratory tract infections (4%). Of deep concern is that 51% of tamariki Māori admitted with diseases of poverty were re-hospitalised (at least once) within the next 6 months. At 12 months, for all causes of admission, the risk of readmission for Māori was 56% (9). At the time of the study, in a reported attempt to drive improvements in health spending, health delivery and health equity, a quality improvement target for the NZ Ministry of Health was developed to reduce readmissions for preventable conditions for tamariki aged 0–4 (10).

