As a response to these issues of unmet health need and inequitable and unacceptable hospital readmission rates for tamariki Māori in the Waikato, Te Puna Oranga (the Māori Health Unit) at Te Whatu Ora Waikato led a co-design process with nurses, Kaitiaki (cultural support workers) and doctors who had worked or were working in child health at Waikato Hospital (11). The co-design process resulted in the development of a tool to identity health and wellbeing needs, and to support opportunities to address need and enable the provision of holistic and preventative care particularly for hospitalised tamariki Māori and their whānau. The Harti Tool was added in a paper folder to patient notes and used in the paediatric medical wards at Waikato Hospital from 2014 to 2017. The paediatric medical charge nurse reported that the majority of patients and their whānau were provided access to a wellbeing needs assessment using the tool during this time.

The team presented the Harti approach to colleagues around the country at peer meetings, conferences and seminars. The tool was shared freely with all people and groups who requested it. As a result, the tool was implemented in other areas around the country. After the Harti tool had been in place for 3 years, the team decided to apply for a Health Research Council of New Zealand grant to measure the impact of the tool. Another driver was the need to update the screening questions and follow up protocols in the tool and to further develop thinking around the model of care for the tool.

This paper describes the protocol for the quantitative evaluation of the effectiveness of the Harti Tool using a randomized controlled trial (RCT). Objectives of the RCT (the “Harti RCT”) are:
➢To provide a quantitative measure of the effectiveness of the Harti tool➢To determine the level of unmet need identified by the Harti tool, and➢To assess the impact of the Harti tool on meeting those needs and achieving improved outcomes for tamariki.

The Harti RCT aims to answer the following research questions compared with usual care;
➢Does the use of the Harti tool increase documentation of assessment of health and non-health needs?➢Does use of the Harti tool result in a lower readmission risk for hospitalised children?➢Does the Harti tool improve satisfaction with hospital experience?➢Does the Harti tool increase access to and utilisation of wellbeing services?

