### Sample size calculation

2.8

We aim to recruit a total of 1,000 participants, of whom we expect approximately 40% will be Māori (based on current figures and expected acceptability of the research protocol). This sample has been calculated to ensure that there is sufficient statistical power to detect a 7% absolute reduction in the 30-day readmission risk in the intervention group for all children and a 12% absolute reduction in the 30-day acute readmission risk for Māori. Sample size calculations are based on a two-tailed 0.05 level of significance with 80% power. We assume that the acceptability of participation will be similar for Māori and non-Māori.

We will measure differences between the intervention and control groups in the primary endpoint (readmission risk) controlling for age, sex, residing in Hamilton, socioeconomic deprivation (NZiDep), and RA responsible for conducting the intervention. Analyses of the primary endpoint will be stratified by ethnicity.

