### Measures of effectiveness

2.12

A summary of each research hypothesis is listed in Table 2 and the details of how these will be examined is below.

**Table 2 T2:** The primary (1, 1a) and secondary endpoint hypotheses summarised for the trial outcome data.

Hypothesis number	Hypothesis
1	Use of the intervention will result in a 7% lower readmission risk at 30-days for children aged 0–4 admitted to hospital for the intervention group compared to the usual care group.
1a	Use of the intervention will result in a 5% lower readmission risk at 30 days for children aged under 12 months admitted to hospital for the intervention group compared to the usual care group.
2	The intervention will result in a 5% higher satisfaction with hospital experience score for the intervention group compared to the usual care group.
3a	Compared to usual care, the intervention assessment will result in at least a 50% increase in the full documentation of non-enrolment with a GP, non-enrolment in oral health services, not up-to-date oral health checks, incomplete immunisation (for age) and incomplete WCTO participation.
3b	Compared to usual care, the intervention assessment will result in at least a 25% increase in full compliance with GP enrolment, oral health service enrolment, oral health checks, immunisation and WCTO participation.
4	Compared to the UC group, the intervention group will have at least a 25% higher complete smoking cessation referral rate for households with a documented resident who smokes.
5	The intervention group will have at least a 25% higher complete Whare Ora referral rate compared with the UC group
6	The intervention group will have a significantly lower median cumulative length of hospital stay in all acute admissions in the 12 months following discharge from the index admission event compared with the UC group
7	The readmission rate in the intervention group will be 25% less than the readmission rate in the UC group.

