### Frequency of readmission

2.21

The frequency of readmission is explored in Hypothesis 7. This endpoint will be calculated as the rate ratio of acute readmission in the 12 months following discharge from the index admission event. It differs from the primary endpoint in using all admissions in the numerator, and a person-time denominator, which will exclude any days in which the patient is in hospital.

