### Data handling and monitoring

2.23

Analysis will be performed on an intention to treat basis. That is, endpoints will be compared for the two groups as defined from the point of randomisation to intervention or control group. For the primary endpoint, participants who are readmitted multiple times from each group will be included in the analysis only for the first (valid) occasion on which they are readmitted in the 12 months following the index admission.

Bivariate analyses comparing groups will test for statistical significance using the Chi Square test for differences in proportions. For the length of stay secondary endpoint where a difference in medians is to be tested, the Mann–Whitney *U* test will be used.

Although the randomised design is expected to yield balanced intervention and control groups in a study of this size, logistic regression analysis will be used for the primary and secondary endpoints to control for important confounding variables and to facilitate the assessment of interaction variables that increase or decrease the efficacy of the Harti tool. Statistical significance will be tested at the alpha level of 0.05. We will control for the false discovery rate in the secondary endpoints using the Benjamini–Hochberg method (39).

The study is not powered to detect ethnic differences in the impact of the intervention (effect modification). However, we will nevertheless conduct exploratory tests for effect modification with ethnicity (Māori/non-Māori), gender (male/female excluding other), and deprivation (as a dichotomised variable) using the Breslow Day test for homogeneity of odds ratio, and standard maximum likelihood methods (likelihood ratio tests) based on binomial regression models. We will assume an additive interaction for these analyses and report the relative excess risk due to interaction (RERI) where this is significant effect.

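### Hypothesis 6 measures cumulative stay by medians that are likely to be 0 v 0 hours overall, and the logistic regression named for all secondary endpoints does not fit H2, H6 or H7

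*Protocol article*

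**What the plan says.** Table 2 (section 2.12) states Hypothesis 6 as a "significantly lower median cumulative length of hospital stay in all acute admissions in the 12 months following discharge". Section 2.20 sets the measure: "This endpoint will be calculated as the difference in median cumulative lengths of stay by individual". It counts only coded acute events of at least 3 hours at hospitals in the Waikato region, and it prefers medians as protection against very long stays. It does not restrict the comparison to readmitted children, and section 2.23 sets analysis by intention to treat.

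Section 2.23 assigns the test: "For the length of stay secondary endpoint where a difference in medians is to be tested", the Mann–Whitney *U* test applies. The same section names logistic regression as the adjusted analysis of the primary endpoint and of the secondary ones, with no exception. Three of those are not binary:

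- H2 is a satisfaction score rescaled to 0–100 (section 2.16).
- H6 is in hours.
- H7 is a person-time rate: "This endpoint will be calculated as the rate ratio of acute readmission in the 12 months following discharge" (section 2.21).

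On readmission, the Introduction reports: "At 12 months, for all causes of admission, the risk of readmission for Māori was 56" per cent. Section 2.8 adds: "We aim to recruit a total of 1,000 participants, of whom we expect approximately 40% will be Māori".

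**The concern.** Cumulative stay after the index discharge has a large mass at zero. If half or more of the children in an arm have no counted readmission, that arm's median is 0 hours however many hours the others spend in hospital. A difference in medians then cannot register bed-hours saved. Where the control median does rise above 0, it sits among the shortest stays and mainly records that readmission has crossed 50%.

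H6 is the trial's bed-use result. As worded, it needs a lower median, so it could go unsupported while the test is significant and hours are in fact reduced.

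The regression sentence raises a second problem. Binary logistic regression cannot return a difference on a 0–100 score, a difference in hours or a person-time rate ratio. Followed literally, it would mean dichotomising these endpoints or dropping the stated measures.

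**Working it through.** **The plan's own figure.** No sample size or power is given for H6. The total of 1,000 belongs to the primary endpoint and cannot be recomputed, because no control risk is stated. It is consistent with 23% v 16% at 30 days (two-sided 0.05, 80% power: N = 1,004). The expected 400 Māori are consistent with 30% v 18% (N = 396). Nothing here shows that 1,000 is wrong.

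**Inputs.** Māori 12-month risk is 56% (Introduction). The Māori share is 40% of 1,000 (2.8). Allocation is 1:1 (2.2), so about 500 per arm. The non-Māori 12-month risk *q* is not given and is varied. The article does treat Māori readmission as the higher rate: "inequitable and unacceptable hospital readmission rates for tamariki Māori".

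**Break-even.** Overall control risk = 0.40 × 0.56 + 0.60 × *q* = 0.224 + 0.60*q*. It equals 50% at *q* = (0.50 − 0.224)/0.60 = 46%.

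**Probability that both medians are 0.** With 500 children, an arm's sample median is 0 when at most 249 are readmitted, so P = P(X ≤ 249), X ~ Binomial(500, risk). The two arms' probabilities are multiplied. The 7-point reduction is the plan's 30-day target, carried to 12 months as an assumption.

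| *q* | Overall control risk | Both medians 0, 7 points lower | Both medians 0, no effect |
|---|---|---|---|
| 30% | 40.4% | 1.00 | 1.00 |
| 35% | 43.4% | 0.998 | 0.997 |
| 40% | 46.4% | 0.94 | 0.89 |
| 44% | 48.8% | 0.69 | 0.47 |
| 46% | 50.0% | 0.48 | 0.23 |
| 50% | 52.4% | 0.13 | 0.02 |
| 56% | 56.0% | 0.002 | 0.000 |

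**A plausible *q*, for illustration only.** The back-solved 30-day risks imply a non-Māori risk of (0.23 − 0.40 × 0.30)/0.60 ≈ 18%. Carrying the non-Māori to Māori ratio to 12 months gives *q* of about 34% (risk scale) to 37% (hazard scale). Overall control risk is then 43–45%, and both medians are 0 with probability about 0.98 or more.

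**Māori alone.** With 56% and 200 per arm, P(control median = 0) = P(X ≤ 99) = 0.038, so the control median exceeds 0 with probability about 0.96.

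**What the rank test does.** Hours among readmitted children were simulated as lognormal (median 48, log-SD 1; assumed), for *q* of 30%, 40% and 46%. Mann–Whitney power was 0.54–0.60 for a 7-point lower risk and 0.90–0.97 for a 25% relative reduction in risk. At *q* = 30% both medians were 0 in every simulated trial, yet power for the 25% reduction was 0.90.

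**What the median hides.** Take 46.4% v 39.4% with the same hours distribution among those readmitted. The probability that an intervention child has fewer hours than a control child, counting ties as half, is 0.606 × 0.464 + ½(0.606 × 0.536) + ½(0.394 × 0.464) = 0.281 + 0.162 + 0.091 ≈ 0.535. Mean hours given readmission are 48 × e^0.5 ≈ 79, so the mean saving is 0.07 × 79 ≈ 5.5 hours per child. The median difference is 0 with probability 0.94.

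**The case against.** The strongest reply is that the prediction rests on a risk the article does not give. That stands. A reader might infer that 0 v 0 is close to guaranteed, and the documents do not support this: at *q* of 44–48% the outcome is uncertain, and at 50% or above it is unlikely. Nor does it follow from the intervention median being 0. With a 25% lower risk that median is 0 even at a control risk of 53%, but both medians are then 0 in only 8% of trials (17% at 52%, 31% at 51%).

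The prediction also fails for Māori alone, a central population of the trial. The article's other figure, "51% of tamariki Māori admitted with diseases of poverty were re-hospitalised (at least once) within the next 6 months", points the same way.

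The test itself survives the ties, so a substantial cut in stay would usually still be detected. What is lost is an informative effect measure and the reading of the test as one of medians.

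On the models, it can be said that the regression sentence is a condensed summary, that it suits the binary endpoints (the primary, H3a, H3b, H4, H5), and that detailed models belong in an analysis plan not shown here. A missing model would indeed be no finding. The point is narrower: the article states a rule for every secondary endpoint, and for three of them the rule does not fit.

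**Conclusion.** The point holds in conditional form. For the whole sample, the declared H6 measure is likely to read 0 v 0 hours if the non-Māori 12-month risk is at most about 43%. It is close to even at 46% and improbable from 50%. The calculation assumes independent children, the 56% figure applied to this trial's Māori participants, and a reduction of 7 points at 12 months. The exclusions in section 2.20 (stays under 3 hours, not case-mix coded, or outside the region) remove hours and push the medians further towards 0.

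Mann–Whitney remains valid as a comparison of distributions. The logistic rule is mis-stated for H2, H6 and H7. A reader might infer that these endpoints cannot be analysed at all. That goes too far, since each has its own stated measure and only the adjusted model is wrong. The primary endpoint is not affected. The correction should be made before unblinded analysis.

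**What to change.** - **H6, in Table 2 and sections 2.20 and 2.23:** restate it as a difference in the distribution of cumulative hours per child, tested by Mann–Whitney. Report the probability index as the effect measure, which keeps the resistance to long stays that section 2.20 wants.
- **Supportive bed-use result:** add the mean difference in hours per child with a bootstrap confidence interval that resamples households, because section 2.7 gives children of one household the same allocation.
- **Description only:** report the proportion with any readmission, and median hours among those readmitted. The latter conditions on a post-randomisation event and is not a randomised comparison.
- **H7:** negative binomial regression with a log person-time offset.
- **H2:** linear regression on the 0–100 score. Use household-clustered robust standard errors for both H7 and H2.
- **Section 2.23:** limit logistic regression to the binary endpoints.

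The cost is a documented change to a declared effect measure in the protocol text, not only analysis-plan wording. No data collection changes. The downside is that the mean stays sensitive to very long stays. A bootstrap interval shows that uncertainty but does not remove it, which is why the mean should be supportive and the probability index should lead.

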### Frequency of readmission

2.21

The frequency of readmission is explored in Hypothesis 7. This endpoint will be calculated as the rate ratio of acute readmission in the 12 months following discharge from the index admission event. It differs from the primary endpoint in using all admissions in the numerator, and a person-time denominator, which will exclude any days in which the patient is in hospital.

### Adverse events

2.22

The only adverse event data collected will be alive status within 12 months of index discharge.

### Data handling and monitoring

2.23

Analysis will be performed on an intention to treat basis. That is, endpoints will be compared for the two groups as defined from the point of randomisation to intervention or control group. For the primary endpoint, participants who are readmitted multiple times from each group will be included in the analysis only for the first (valid) occasion on which they are readmitted in the 12 months following the index admission.

Bivariate analyses comparing groups will test for statistical significance using the Chi Square test for differences in proportions. For the length of stay secondary endpoint where a difference in medians is to be tested, the Mann–Whitney *U* test will be used.

Although the randomised design is expected to yield balanced intervention and control groups in a study of this size, logistic regression analysis will be used for the primary and secondary endpoints to control for important confounding variables and to facilitate the assessment of interaction variables that increase or decrease the efficacy of the Harti tool. Statistical significance will be tested at the alpha level of 0.05. We will control for the false discovery rate in the secondary endpoints using the Benjamini–Hochberg method (39).

The study is not powered to detect ethnic differences in the impact of the intervention (effect modification). However, we will nevertheless conduct exploratory tests for effect modification with ethnicity (Māori/non-Māori), gender (male/female excluding other), and deprivation (as a dichotomised variable) using the Breslow Day test for homogeneity of odds ratio, and standard maximum likelihood methods (likelihood ratio tests) based on binomial regression models. We will assume an additive interaction for these analyses and report the relative excess risk due to interaction (RERI) where this is significant effect.

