### Primary endpoint

2.13

The primary endpoint is the relative risk of an acute hospital readmission in the 30 days following discharge for intervention group patients compared with control group patients (Hypothesis 1). The relative risk of readmission rather than readmission rate ratio was chosen as the primary endpoint because risk (probability of readmission within specified period) is easier to measure as it just requires counting the first time a patient is readmitted. By only counting the first readmission we avoid patients with large numbers of readmissions having a disproportion impact on the endpoint measure. This also simplifies statistical analysis. We have included the hazard ratio of readmission as a secondary endpoint (see below).

We will measure ethnic-specific differences in the primary endpoint measures and differences according to a 30-day^2^ readmission risk for Māori and non-Māori patients (combined).

To determine the superiority limit for the purposes of sample size calculations it was considered that the Harti programme should deliver at least a 7% absolute decrease in overall readmission risk as this would be both clinically meaningful for tamariki and whānau and financially meaningful for the hospital. Furthermore, we have designed the study so that it has power to detect a 12% absolute decrease in the 30-day risk of readmission for the Māori population. It is not powered to detect differences in risk of readmission between Māori and non-Māori tamariki.

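### The declared endpoint is a relative risk, but the only model named for the adjusted comparison yields an odds ratio; the exploratory interaction work mixes an odds-ratio test with an additive assumption and reports RERI only when significant

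*Protocol article*

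**What the plan says.** All references are to the protocol article.

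- **Endpoint scale.** Section 2.13: "The primary endpoint is the relative risk of an acute hospital readmission in the 30 days following discharge for intervention group patients". The comparator is the control arm. The section explains this choice against a rate ratio: "The relative risk of readmission rather than readmission rate ratio was chosen as the primary endpoint".
- **Design target.** Section 2.8 sizes the trial to "detect a 7% absolute reduction in the 30-day readmission risk in the intervention group for all children", and for a "12% absolute reduction in the 30-day acute readmission risk for Māori". Both are risk differences.
- **Adjustment.** Section 2.8 says the primary endpoint comparison will control for age, sex, Hamilton residence, NZiDep deprivation and research assistant, and will be stratified by ethnicity. Section 2.23 names the model: "logistic regression analysis will be used for the primary and secondary endpoints to control for important confounding variables".
- **Unadjusted test.** Section 2.23 compares proportions with a chi-square test.
- **Effect modification.** Section 2.23 plans exploratory tests for ethnicity, gender and dichotomised deprivation, "using the Breslow Day test for homogeneity of odds ratio", together with likelihood ratio tests from binomial regression whose link is not stated. It continues: "We will assume an additive interaction for these analyses and report the relative excess risk due to interaction (RERI) where this is significant effect". The same paragraph says the study lacks power for ethnic differences in effect.

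**The concern.** Covariate adjustment is part of how section 2.8 says the primary endpoint will be measured, so the adjusted estimate is likely to be prominent in the report. As written, that estimate would be an odds ratio, which is neither the declared relative risk nor the risk difference used to size the trial. When the event is not rare, an odds ratio read as a relative risk exaggerates the effect. Odds ratios are also non-collapsible: adjusting for prognostic covariates can move them even when the arms are perfectly balanced, so the crude and adjusted results would not be directly comparable.

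The interaction paragraph has a separate problem. Homogeneous odds ratios and absence of additive interaction are different null hypotheses, and one can hold while the other fails. Reporting RERI only when it reaches significance, in a trial that says it is underpowered for the question, means the estimate would usually go unreported and would tend to be exaggerated when it does appear.

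**Working it through.** **1. The plan's own figure.** Section 2.8 gives 1,000 participants, about 40% Māori, and "Sample size calculations are based on a two-tailed 0.05 level of significance with 80% power". Section 2.2 gives 1:1 allocation, so 500 per arm overall and about 200 per arm for Māori. No 30-day control risk is stated; the Introduction gives only longer-term risks for Māori (51% at 6 months after admission with diseases of poverty, 56% at 12 months for all causes). The 1,000 can therefore be neither confirmed nor refuted. Solving backwards with the pooled-variance formula, where p0 and p1 are the control and intervention risks, p̄ is their mean and d = p0 − p1:

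n per arm = [1.96 √(2p̄(1−p̄)) + 0.8416 √(p0(1−p0) + p1(1−p1))]² / d²

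- d = 0.07 and n = 500 imply p0 ≈ 22.9%. Check: (1.096 + 0.469)² / 0.0049 ≈ 500.
- d = 0.12 and n = 200 imply p0 ≈ 30.4%. Check: (1.191 + 0.506)² / 0.0144 ≈ 200.

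These are assumptions obtained by taking the sample size as exactly right, so a range is shown below.

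**2. Odds ratio against relative risk.** RR = p1/p0, and OR = [p1/(1−p1)] / [p0/(1−p0)] = RR × (1−p0)/(1−p1). When the intervention lowers risk, the last factor is below 1, so OR < RR at any control risk.

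| Assumed risks | RR | OR | Reduction read from RR | Reduction read from OR |
|---|---|---|---|---|
| 15% to 8% | 0.533 | 0.493 | 47% | 51% |
| 20% to 13% | 0.650 | 0.598 | 35% | 40% |
| 23% to 16% | 0.696 | 0.638 | 30% | 36% |
| 30% to 23% | 0.767 | 0.697 | 23% | 30% |
| 50% to 43% | 0.860 | 0.754 | 14% | 25% |
| Māori, 30.4% to 18.4% | 0.605 | 0.516 | 39% | 48% |

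Worked line: 0.16/0.23 = 0.696; (0.16/0.84)/(0.23/0.77) = 0.1905/0.2987 = 0.638.

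**3. Breslow-Day against additive interaction.** All risks in this step are illustrative. RERI takes the lowest-risk cell (intervention, lower-risk stratum) as reference.

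- *No additive interaction, but odds ratios differ.* A 7-point fall in strata with control risks of 15% and 25% gives 8% and 18%. RERI = 25/8 − 15/8 − 18/8 + 1 = 0. The odds ratios are 0.493 and 0.659, so Breslow-Day's null is false.
- *Common odds ratio, but additive interaction present.* An odds ratio of 0.6 in the same strata gives 9.57% and 16.67%, so risk differences of −5.4 and −8.3 points. RERI = (25 − 15 − 16.67)/9.57 + 1 = 0.30. Breslow-Day's null is true.
- *A second example of the latter.* A common odds ratio of 0.65 takes 31% to 22.6% (−8.4 points) and 20% to 14.0% (−6.0 points).

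**The case against.** Several parts of the opposing case stand.

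- A reader might infer that the primary test itself is on the wrong scale. The documents do not support that. The crude relative risk comes straight from the arm proportions, and no effect means the same thing for a risk difference, relative risk or odds ratio. The chi-square test also fits the absolute design target.
- A reader might infer that the additive scale goes untested. That is also too strong. Section 2.23 lists likelihood ratio tests from binomial regression, which can use an identity link, and RERI is itself an additive-scale measure. The fair criticism is that Breslow-Day does not match the stated assumption and that the link is left open.
- A reader might infer that results for Māori could disappear behind a non-significant interaction. Sections 2.8 and 2.13 plan ethnic-specific results for the primary endpoint with no significance condition; only RERI carries one. The interaction work is declared exploratory.
- The protocol does not say that the odds ratio will be presented as a relative risk, so overstatement depends on how the result is read. The control risks used here are not the plan's.

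It can also be said that standardisation after a logistic model is compatible with section 2.23, and that a fuller analysis plan, not shown, may specify it. This softens the point without removing it. The article does fix a model for the adjusted primary endpoint, and the model's direct output is not the declared measure.

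**Conclusion.** The concern holds in a limited form and should be fixed before analysis. The named adjusted model does not by itself deliver the declared relative risk or the risk difference used for sizing. That the odds ratio exaggerates a beneficial relative risk follows from algebra and does not depend on the control risk. The size does: across assumed control risks of 15% to 50% with a 7-point fall, the apparent relative reduction grows by about 4 to 11 percentage points (47% to 51% at the low end, 14% to 25% at the high end), and by about 6 points at the back-solved 23%. The sample size is unaffected.

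The interaction part is secondary because it is exploratory. Within it, the mismatch between Breslow-Day and the additive assumption and the significance-dependent reporting of RERI are both in the text and depend on no assumed figure.

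**What to change.** 1. State that the adjusted primary result is a relative risk and a risk difference, each with a 95% CI. Suitable routes for the relative risk are log-binomial regression or modified Poisson regression with robust standard errors. Marginal standardisation after the logistic model gives both measures, so the named model can stay if that step is added.
2. Replace Breslow-Day with an additive-scale estimate: the group-by-modifier term from an identity-link model, a standardised difference in risk differences, or RERI. Alternatively, keep it and label it as a multiplicative-scale test. State the link for the binomial regression models.
3. Report the interaction estimate with its 95% CI for ethnicity, gender and deprivation whatever the p-value.

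The cost is a few sentences in the analysis plan and a few lines of code. No new data are needed and the sample size does not change.
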